### Randomization and blinding

Block randomization will be implemented for this study, with varying block sizes of 2 to 4, to prevent selection bias and predictability. The randomisation list will be computer-generated and concealed by a researcher (author identifying information) who will have no direct contact with the participants. A research assistant will enroll participants and assign them to either the “Taekwondo training with elements of music therapy” (n = 36) or the “Taekwondo training alone” (n = 36) group in a 1:1 ratio. Given the behavioral nature of the intervention, blinding will not be feasible for the participants and parents. They will be unaware of their group allocation in the recruitment process until they provide written consent. The coaches, the trial coordinators, and the research personnel who review and code the video recording of the training sessions will also not be blinded to the group allocation. There will be concealment of the allocation sequence so that the trial coordinators will not know the group allocation of an individual before they consent them. To minimize measurement bias, all other research personnel involved in data collection, processing, and analysis will be blinded to group allocation.

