#### 2. Overall effects of the Taekwondo training program

The following assessments will be conducted by an assessor experienced in the measurement tests and blinded to group allocation at baseline, after completion of the 10-week program, and at 2-month follow-up at the university laboratory and the Taekwondo training center.

*2*.*1 Gross motor skills*. The assessment will include gross motor composites that measure manual coordination, body coordination, and strength and agility from the Bruininks–Oseretsky Test of Motor Proficiency-2 (BOT-2) [41]. Manual coordination will be evaluated through two tasks that test upper-limb coordination. Body coordination will be assessed through seven tasks that test bilateral coordination and nine tasks that test balance. Strength and agility will be evaluated through five tasks that assess running speed and agility and five tasks that evaluate strength. A trained assessor will demonstrate each item to the children during the assessment. Visual aids will be displayed on an easel for the children’s reference. The raw scores of each task will be converted to the point scores. The point scores for each task within the same gross motor composite will be added up as a sub-score. This allows for comparisons to be made across different assessment times. The BOT-2 had good test-retest reliability and internal consistency of the total scale, with an ICC of 0.99 (95% confidence interval) and Cronbach’s alpha coefficient of 0.92 [42].

*2*.*2 Taekwondo skills performance*. A scoring system was modified for use in this project with reference to the international Taekwondo referee scoring standard. This assessment will be carried out at the Taekwondo training center. Children’s performance for a set of selected Taekwondo moves and kicks will be observed and scored by two qualified referees. Both accuracy and overall presentation of the Taekwondo movement, stance, and techniques will be scored.

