### Sample size calculation

A previous study that used jogging as an exercise format in a group of children with ASD aged 5 to 13 years demonstrated that the percentage of time the participants spent in vigorous exercise, which correlates with engagement, was significantly higher under the slow-music condition (a tempo of 60, which is similar to the songs developed in this proposal) compared with the non-music condition (mean difference = 11.8%, common SD = 21.6%, effect size d = 0.55) [26]. Another study also revealed that music increased the engagement of students with autism during group activities [18], as the percentage of time in class during which participants exhibited active engagement behaviors increased from 44.7% ± 16.9% to 68.8% ± 13% (effect size d = 1.61). Considering these studies, assuming an effect size (d) of at least 0.55 in the primary outcome proposed for this study (engagement) will be observed for the Taekwondo training with elements of music therapy condition in contrast to the Taekwondo training alone condition, a minimum of 54 subjects are required to detect such an effect with a power of 80% and type I error of 0.05. To account for a 20% attrition rate and the requirement of pairing-up children for practice per group, 72 participants will be recruited in total.

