### Statistical analysis

The participants’ characteristics and primary and secondary outcomes will be evaluated using summary statistics, including mean (SD), median (IQR), or proportions as appropriate, at multiple time points. The primary analysis will consist of an intention-to-treat analysis comparing the primary outcome (engagement) between the two intervention groups; specifically, a linear mixed-effect model will be used to investigate the effect of intervention (Taekwondo training with vs without elements of music therapy) over time (interaction between intervention and time) on the engagement in the training sessions, with a random effect for each participant. The effects of music therapy on the secondary outcomes measured during the training sessions, including physical activity levels, enjoyment state, and the rate of perceived exertion, will be tested by independent samples t-tests. Further, we will use a linear regression model to investigate the effect of intervention on these outcomes, adjusting for the following prognostic variables: age, sex, and BMI. A log transformation will be applied for any outcomes resulting in a skewed distribution.

For the other secondary outcomes measured before and after the training sessions, a linear mixed-effect model will be used to investigate the effect of intervention over time (interaction between intervention and time), with a random effect for each participantand adjusting for the following prognostic variables: age, sex, and BMI. The analyses will also evaluate the sustained benefits of the training by assessing the effect of the intervention on the secondary outcomes at the 2-month follow-up using the statistical methods described above. The significance level will be set at *p*< .05, and all analyses will be performed using SPSS (v25.0 for Windows; IBM, Armonk, NY, USA).

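### For the pre/post secondary outcomes, adjusting the mixed model for age, sex and BMI as main effects barely touches the intervention-by-time effect being tested, so that effect is in practice unadjusted

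*Protocol article*

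**What the plan says.** Under Statistical analysis, the article says of the secondary outcomes measured before and after training that "a linear mixed-effect model will be used to investigate the effect of intervention over time (interaction between intervention and time"). The same sentence goes on to specify the random part and the covariates of this model: "with a random effect for each participantand adjusting for the following prognostic variables: age, sex, and BMI". It names no covariate-by-time term and does not say whether BMI is a baseline value or is measured again at each visit.

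The later time point inherits this model, because sustained benefit is to be judged by "assessing the effect of the intervention on the secondary outcomes at the 2-month follow-up using the statistical methods described above". The section on overall effects gives three assessments, with an assessor "blinded to group allocation at baseline, after completion of the 10-week program, and at 2-month follow-up".

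The outcomes recorded during sessions are handled differently. After t-tests, "we will use a linear regression model to investigate the effect of intervention on these outcomes, adjusting for the following prognostic variables: age, sex, and"; the third covariate in that list is again BMI. That model contains no time interaction. The primary engagement model lists no covariates.

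**The concern.** The same three covariates and the same adjusting phrase appear in two kinds of model. In the in-session regression, the adjustment acts on the intervention effect. In the mixed model the quantity tested is a difference between arms in change over time, and a covariate that is constant within a child and enters only as a main effect says nothing about change.

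The trial could therefore report effects on motor skills, executive function and psychosocial outcomes as adjusted for prognostic variables when the adjustment has hardly reached them. This could matter for age. The children are 7 to 9 years old, the randomisation section describes blocks but no stratification by age or sex, and the motor test is analysed as summed point scores with no age standardisation described. If older children gain more and the arms happen to differ in age, the stated model leaves that difference in the result.

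**Working it through.** **Inputs from the article.** Tested effect: intervention by time. One random effect per participant. Covariates: age, sex, BMI. Three visits. Arms of 36 ("Taekwondo training alone” (n = 36) group in a 1:1 ratio"). Attrition of 20%, from the sample size section. The article gives no figure of its own on this point, since its sample size concerns engagement, and it gives no variances or covariate effects for these outcomes. Those used below are assumptions.

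**Step 1, algebra.** For child i at visit j, with arm g and time-constant covariates x:

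Y_ij = m_j + a·g_i + d_j·g_i + b·x_i + u_i + e_ij

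Subtracting baseline:

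Y_ij − Y_i0 = (m_j − m_0) + d_j·g_i + (e_ij − e_i0)

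Both b·x_i and u_i are gone. With every visit observed, the estimate of d_j is the difference between arms in mean change, whatever b is. Its standard error (SE) is s_e × √2 × √(1/36 + 1/36), where s_e is the within-child SD.

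**Step 2, check of the SE.** With s_e = 0.6 (assumed): 0.6 × 1.414 × 0.2357 = 0.200. The mean fitted SE was 0.197.

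**Step 3, simulated trials.** These had 72 children and three visits, fitted by REML with a random intercept. Assumptions: age uniform over 7 to 10, level rising 0.5 per year of age, 0.4 for sex and 0.1 per BMI unit, between-child SD 0.5, outcome SD about 1. The covariates predict level but not gain. The table compares the interaction estimate with and without the covariate main effects.

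| Data | Mean absolute difference | Largest difference | SE without | SE with |
|---|---|---|---|---|
| Complete (40 trials) | 1.3e-14 | 3.4e-14 | 0.197 | 0.197 |
| 20% of children lost after baseline (40 trials) | 0.016 | 0.057 | 0.2148 | 0.2131 |
| 20% of later visits missing (40 trials) | 0.019 | 0.057 | 0.2138 | 0.2128 |
| Complete, BMI re-measured each visit (30 trials) | 0.009 | not recorded | not recorded | not recorded |

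With children lost, the average shift is 0.016 / 0.2148 = 0.07 SE, the largest in any one trial is 0.057 / 0.2148 = 0.27 SE, and the SE falls by 0.8%. A separate set of simulated trials gave a mean shift of 0.007 against an SE of 0.18, or 0.04 SE.

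This is not because the covariates were weak. In the same complete-data fits, the baseline difference between arms moved by 0.094 on average and its SE fell from 0.223 to 0.186. The adjustment works on level but does not reach change.

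**Step 4, what an imbalance would leave behind.** If ages are uniform over 7 to 9.99, their SD is 2.99/√12 = 0.863, and the SE of the age difference between arms is 0.863 × √(2/36) = 0.20 years. The shift left in the interaction is the age gap times the extra gain per year of age (both assumed):

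| Age gap (years) | Slope 0 | Slope 0.10 | Slope 0.20 | Slope 0.35 |
|---|---|---|---|---|
| 0.20 | 0 | 0.02 | 0.04 | 0.07 |
| 0.30 | 0 | 0.03 | 0.06 | 0.105 |
| 0.40 | 0 | 0.04 | 0.08 | 0.14 |

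Simulating a gap of 0.3 and a slope of 0.35 with a true effect of 0.30 (60 trials) gave mean estimates of 0.403 without covariates, 0.403 with main effects, and 0.288 with covariate-by-visit terms. With 20% dropout they were 0.365, 0.368 and 0.274.

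**Step 5, price of the remedy.** Adding covariate-by-visit terms raised the SE from 0.197 to 0.201 (2%) when the covariates did not predict gain. At the slope of 0.35 it fell from 0.1592 to 0.1549 (2.7%) in one set of simulated trials and by about 6% in another.

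**The case against.** The article says only that the model adjusts for three variables. It does not exclude covariate-by-time terms, and a full analysis plan may contain them. That is fair, and nothing here is raised as missing. The point is about an adjustment the article does state: on its plain meaning, that adjustment does not act on the effect named in the same sentence.

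Four stronger readings are tempting, and the document does not support them.

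- **The covariates cancel exactly.** This needs complete visits and time-constant covariates. The article plans for 20% attrition and leaves the timing of BMI open, so the two analyses will differ slightly. With missing visits the covariates may also help make a missing-at-random assumption more plausible.
- **The reported effects are biased.** Allocation is randomised, so the unadjusted interaction is unbiased on average. The contrast of 0.40 with 0.29 fixes one age gap in every trial. A gap of that size is about 1.5 SE, which chance would reach in either direction in roughly 14% of trials. The assumed slope, 0.35 per year, exceeds the assumed treatment effect of 0.30, and nothing in the article supports a slope that steep.
- **Precision is being thrown away.** Step 5 shows that covariate-by-visit terms can lower or raise the SE.
- **The whole analysis is affected.** The primary model lists no covariates, and in the in-session regressions the adjustment does act.

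**Conclusion.** The concern holds in a limited form. For the pre/post secondary outcomes, including the 2-month effect, main-effect adjustment for age, sex and BMI has no influence on the intervention-by-time effect with complete data. With the planned attrition it has very little: 0.04 to 0.07 SE on average when children are lost after baseline. The effect is in practice unadjusted.

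This rests on the main-effects reading, a random intercept per child and covariates fixed within child. The sizes under attrition also depend on the assumed variances. The test remains valid and its error rate is not inflated. What is lost is correction of a chance imbalance in a variable that predicts change: anywhere from nothing to 0.14 outcome units over the range shown. The consequence is modest and confined to these secondary outcomes, but the remedy is cheap enough to be worth making.

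**What to change.** In the mixed models for the pre/post secondary outcomes, enter baseline age, sex and BMI together with their interactions with visit. Wording such as the following would do: fixed effects are intervention, visit, intervention by visit, baseline age, sex and BMI, and each of these three by visit, with a random intercept per child. The adjustment then acts on the change being tested, and the timing of BMI is settled. If the team prefers the simpler model, it should not describe the interaction effects as adjusted for these variables.

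The cost is one line of specification and no new data. The model gains three parameters per follow-up visit, six over the two follow-up visits, in 72 children, with an SE about 2% larger if the covariates turn out not to predict change.

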## Discussion

In this project, we propose to evaluate the impact of incorporating music therapy into a 10-week Taekwondo training intervention designed specifically for children with ASD. Autism is a lifelong condition that begins in childhood and can affect the quality of life of the affected child and their family; therefore, the current project aims to design and test an intervention that promotes long-term participation. An intervention incorporating exercise and music is non-invasive, relatively inexpensive to other conventional interventions, and enjoyable. Furthermore, an abundance of evidence demonstrates that exercise and music can improve the symptoms of ASD, and the influence of exercise training on the affected children’s physical and mental health will be long-lasting if they exercise regularly.

Compared to the ‘Taekwondo-only’ group, those in the ‘Taekwondo with music therapy elements’ group are expected to have greater physical activity levels, enhanced engagement and enjoyment, and lower rates of perceived exertion during the training sessions. These children are predicted to demonstrate greater improvement in physical function (gross motor skills and sports performance) and mental function (attention, social communication, and behaviors) after receiving the 20-session Taekwondo training with music therapy elements. Furthermore, some of the children who participate in this program may choose to take part in regular Taekwondo practice and pursue it as a lifelong passion. Parents will be able to observe the overall effects of the 20-session Taekwondo training under different conditions (i.e., the presence or absence of music) on their child, which will inform their future planning of their children’s physical activities. Moreover, parents who observe their children’s improvement during the program may relieve parental stress and improve parental efficacy.

The findings of this study will contribute an additional option for managing children with ASD and evidence-based strategies that can enhance children’s active engagement in training sessions. The findings will benefit educational work and offer potential practical suggestions for teachers and health professionals to enhance teaching and training efficacy in children with ASD.

### Protocol amendments

Any necessary protocol changes will be effectively communicated and modified in the relevant parties (institutional review board, trial registry, and journal).
